## Methods

### Study timeline

Year 1 will focus on planning and collaborative work with two schools, in Seattle, WA and Miami, FL, to pilot school-specific implementation plans. In years 2 through 4, we will conduct a randomized controlled trial comparing (1) STRIPES to (2) SSU + . In each of the three annual cohorts, 24 9th grade students will be recruited at each of the two schools (12 per condition; total *N* = 144) and will be randomized within school and cohort using permuted block randomization. Teachers who nominate students will obtain written parental permission to nominate, a demographic form, and a DSM-5 ADHD checklist [32]. A core academic teacher completes the same ADHD checklist and impairment measures (IRS; [69, 70]). Ninth grade students will be eligible to participate if they display at least 4 symptoms of inattention or hyperactivity/ impulsivity and elevated academic impairment, defined as meeting two of the following: (1) D or F in an academic class, (2) at least 20% of assignments missing in a class, (3) “3” or higher on the teacher IRS academic impairment item (0-6 scale; [70]), (4) elevated score on the teacher Adolescent Academic Problems Checklist (AAPC; 4 items endorsed “pretty much/very much;” [69]). Students are excluded if placed in special education classes, as this study aims to test a low-cost intervention in general education settings. Students with comorbid learning disabilities will be eligible if placed in general education classes. Peer interventionists will be nominated by teachers and must have at least a 3.0 GPA and no suspensions during the past 12 months. Written parental consent and youth assent will be required [70].

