Analyses will adhere to Consolidated Health Economic Evaluation Reporting Standard recommendations [98]. Costs will be compiled for each trial arm at the student, school, and district levels. Cost-effectiveness analysis is the preferred evaluation method for interventions involving well-defined, non-monetary outcome measures [99]. This method does not require that the effectiveness measure be translated into dollars, and it allows for comparisons across multiple interventions if they have common outcomes of interest. The primary learner outcomes for cost effectiveness analyses will be class attendance and GPA. In cases where one treatment arm is both more costly and more efficacious, incremental cost-effectiveness ratios (ICERs) will be computed. The ICER reports the additional cost of achieving a one-unit improvement in the outcome measures relative to the next least expensive tier. When there are statistically significant differences in outcomes, cost-effectiveness acceptability curves will be constructed to account for variability in the cost and outcome data. These curves yield the probability of one treatment being preferred over another assuming different threshold levels for the value of a unit of outcome improvement [100]. Additional one-way and probabilistic sensitivity analyses will be conducted as needed.

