#### Statistical power

We estimate 5% attrition based on previous studies. Statistical models are outlined in Fig. 2. Aim 2. Based on simulations by Fan [101], we assessed statistical power for mixed models, given a fixed sample size of 144. Based on previous research [44], we expect group differences at later time points to range from medium to very large (*d* = 0.47, 0.85, 1.11, 1.47, 1.69, 2.05 for primary outcomes); Fan [101] found that statistical power exceeded 0.80 with samples of about 100 with medium or larger effects. Aim 3. For the indirect effects proposed in Aims 3a-3c, statistical power estimates are based on sample size calculations by Fritz and MacKinnon [102]. Statistical power for the indirect effect depends entirely on the values of the “a path” (X to M effect) and “b path” (M to Y effect) effect sizes. With a sample size of 144 and using preferred bootstrap methods, we have sufficient power to detect the indirect effect provided both the “a path” and the “b path” are greater than *d* = 0.35. Prior research [44] shows “a paths” for Aims 3a and 3b that range from *d* = 0.85 to 2.05. Aim 4. We will assess statistical power of the cost-effectiveness analysis using methods outlined by Boyd and colleagues [103]. Aim 5. Due to the complexity of estimating statistical power for the mixed models in Aim 5, we base our estimates of power on effects from the previous STRIPES trial [44], which used similar models for analysis with a substantially smaller sample. We used F statistics to estimate the non-centrality parameter, estimated a denominator degrees of freedom based on more observations (144 students each measured 5 times versus 72 students each measured 4 times), and estimated statistical power for a generic F test based on these values. Of the 35 effects examined, the mean power value was 0.61. Seven effects had estimated power > 0.80; based on the non-centrality parameters for these effects, we have adequate power to detect effects as small as Cohen’s *d* = 0.245, which is a small effect size.

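### Aim 4 builds acceptability curves only after a significant outcome difference, so an ICER may be reported with no committed statement of its uncertainty

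*Protocol article*

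**What the plan says.** All the rules at issue stand in the protocol article, Data analysis plan, Aim 4.

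- Outcomes: "The primary learner outcomes for cost effectiveness analyses will be class attendance and GPA".
- Trigger for the ICER: "In cases where one treatment arm is both more costly and more efficacious, incremental cost-effectiveness ratios (ICERs) will be computed". No significance condition is stated.
- Trigger for the acceptability curve: "When there are statistically significant differences in outcomes, cost-effectiveness acceptability curves will be constructed to account for variability in the cost and outcome data".
- Purpose of the curve: "These curves yield the probability of one treatment being preferred over another assuming different threshold levels for the value of a unit of outcome improvement".
- Other uncertainty work: "Additional one-way and probabilistic sensitivity analyses will be conducted as needed". Nothing says what would make it needed.

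The Statistical power section gives no figure for Aim 4. It says only that power for the cost-effectiveness analysis will be assessed by a cited method.

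**The concern.** An acceptability curve describes joint uncertainty: how probable it is, given the data on costs and effects, that one arm is the better choice at each value placed on a unit of outcome. The plan describes it in these terms itself. Tying it to a significant outcome difference works against that purpose in three ways.

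1. The curve is withheld when the outcome evidence is uncertain, which is when a reader most needs to see that uncertainty.
2. The condition looks at outcomes only. Costs vary between students and schools whether or not GPA or attendance differs significantly. If outcomes are similar, cost uncertainty largely decides the question for a school.
3. The ICER and the curve have different triggers as written. A gain in GPA that is not significant, at higher cost, can produce an ICER while the curve that would qualify it is not called for.

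At stake is what schools and districts are given when they decide whether to adopt STRIPES: a ratio with its uncertainty, or possibly a ratio alone.

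**Working it through.** **Inputs from the protocol article.** Sample size: "given a fixed sample size of 144" (Statistical power). Allocation: "12 per condition" in each of 2 schools and 3 cohorts (Study timeline), so 2 × 3 × 12 = 72 per arm. Attrition: "We estimate 5% attrition based on previous studies" (Statistical power), so 72 × 0.95 = 68.4 per arm. Anticipated effects: d from 0.47 to 2.05 (Statistical power). The article does not say which d belongs to GPA or to attendance.

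**Assumptions.** Two-sided alpha 0.05 (the article states no alpha), a simple comparison of two means with SD 1, no clustering, normal approximation.

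**The plan's own figure.** Aim 4 has none. The nearest is the Aim 2 statement that power exceeds 0.80 with about 100 students for medium or larger effects.
- At N = 100 and d = 0.5, a plain comparison gives Φ(0.5/√(2/50) − 1.96) = Φ(0.54) = 0.705.
- With baseline adjustment at an assumed correlation of 0.5, the SD falls to √0.75 and power is 0.823.

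The statement is therefore attainable with a standard adjusted analysis.

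**Chance that no curve is built.** With SE = √(2/n) for n per arm, P(no curve) = 1 − Φ(d/SE − 1.96). The opposite tail is negligible here. SE is √(2/72) = 0.167 with everyone and √(2/68.4) = 0.171 after attrition.

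| True d | No curve, 72 per arm | No curve, 68.4 per arm |
|---|---|---|
| 0.30 (assumed, below planning range) | 1 − 0.436 = 56% | 1 − 0.419 = 58% |
| 0.47 (smallest planned) | 1 − 0.805 = 19.5% | 1 − 0.785 = 21.5% |
| 0.85 (next planned) | 0.1% | 0.1% |

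For example, at d = 0.47 with 72 per arm: 0.47/0.167 = 2.82, 2.82 − 1.96 = 0.86, and Φ(0.86) = 0.805.

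A more efficient analysis lowers these figures. With the same assumed baseline correlation of 0.5, power at d = 0.47 is 0.903 (72 per arm) or 0.888 (68.4 per arm), so a curve is missing in about 10% to 11%.

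**What a withheld curve would have shown.** As the value placed on a unit of outcome grows, the curve tends to the probability that the effect is positive, which is Φ(z) under a normal approximation.
- At z = 1.28 (two-sided p = 0.20) it tends to 0.90.
- At z = 1.5 (p = 0.13) it tends to 0.93.

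At a value of zero, the curve is simply the probability that STRIPES costs less, which does not involve the outcome test at all. A non-significant result can thus give an informative curve, and the rule would withhold it.

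**The case against.** Several objections are fair.

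**Uncertainty analysis does not disappear.** A reader might infer that a non-significant result leaves no uncertainty analysis at all. The documents do not support that: one-way and probabilistic sensitivity analyses remain possible, and a fuller analysis plan may say more. They are discretionary with no stated trigger, however, so the curve is the only uncertainty analysis with a stated trigger, and that trigger is the significance test.

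**The ICER trigger is ambiguous.** The article does not say whether superior efficacy is judged on point estimates or on a test. If on a test, the ICER and the curve may open together and the unaccompanied ICER largely goes away. The condition on the curve would still be there. The mismatch is therefore a possibility under the wording, not an established contradiction.

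**Selection on significance.** A reader might infer that the curves shown will overstate cost-effectiveness. Across hypothetical repetitions, estimates that pass the test are too large on average: about 1.12 to 1.14 times at d = 0.47 and essentially 1.00 at d = 0.85. But any significant result carries this, with or without a curve. Removing the condition changes no curve that would have been shown, so this argument does not support the fix and is not relied on here.

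**The percentages are illustrative.** The plan specifies mixed models with covariates, and school outcomes are collected at five time points, so the chance of significance may differ. The text also leaves open whether one significant outcome of the two is enough.

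A further inference, that the plan treats a non-significant difference as zero, has no support: the article does not say what would be concluded in that case.

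**Conclusion.** The point holds in a limited form. The significance condition is an explicit rule in the article, not a detail left out of it, and it conflicts with the curve's own stated purpose. It can leave an ICER without a committed statement of uncertainty.

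Under the assumptions listed, about one trial in five would lack a curve if the true effect equals the smallest planned value, and practically none at the larger planned values. Above half is reached only for effects such as d = 0.30, which is a scenario of this review and not a planning value. Because no d is tied to GPA or attendance, the article gives no assurance about which case applies.

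The reach is confined to one part of Aim 4. Randomisation, data collection and the Aim 2 effect tests are untouched. The change should be made, but the trial does not depend on it.

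**What to change.** Delete the significance condition in Aim 4. State that an acceptability curve will be built from the joint distribution of cost and effect differences, for example by bootstrap, for both GPA and class attendance, whatever the p-value. It would help to say in the same sentence whether the ICER's efficacy criterion refers to the point estimate.

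Other displays, such as a cost-effectiveness plane, net benefit or a confidence region for the ICER, are optional and not needed to cure this defect.

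The cost is a line or two of wording and some routine extra analysis of cost and outcome data already planned for collection.

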#### Statistical power

We estimate 5% attrition based on previous studies. Statistical models are outlined in Fig. 2. Aim 2. Based on simulations by Fan [101], we assessed statistical power for mixed models, given a fixed sample size of 144. Based on previous research [44], we expect group differences at later time points to range from medium to very large (*d* = 0.47, 0.85, 1.11, 1.47, 1.69, 2.05 for primary outcomes); Fan [101] found that statistical power exceeded 0.80 with samples of about 100 with medium or larger effects. Aim 3. For the indirect effects proposed in Aims 3a-3c, statistical power estimates are based on sample size calculations by Fritz and MacKinnon [102]. Statistical power for the indirect effect depends entirely on the values of the “a path” (X to M effect) and “b path” (M to Y effect) effect sizes. With a sample size of 144 and using preferred bootstrap methods, we have sufficient power to detect the indirect effect provided both the “a path” and the “b path” are greater than *d* = 0.35. Prior research [44] shows “a paths” for Aims 3a and 3b that range from *d* = 0.85 to 2.05. Aim 4. We will assess statistical power of the cost-effectiveness analysis using methods outlined by Boyd and colleagues [103]. Aim 5. Due to the complexity of estimating statistical power for the mixed models in Aim 5, we base our estimates of power on effects from the previous STRIPES trial [44], which used similar models for analysis with a substantially smaller sample. We used F statistics to estimate the non-centrality parameter, estimated a denominator degrees of freedom based on more observations (144 students each measured 5 times versus 72 students each measured 4 times), and estimated statistical power for a generic F test based on these values. Of the 35 effects examined, the mean power value was 0.61. Seven effects had estimated power > 0.80; based on the non-centrality parameters for these effects, we have adequate power to detect effects as small as Cohen’s *d* = 0.245, which is a small effect size.

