### Data analysis plan

Analyses will be performed using Mplus version 7 or higher. Missing data will be handled with full information maximum likelihood estimation.

#### Aim 2

The direct effect of STRIPES on each variable (GPA, class attendance, AM, EF) will be evaluated using mixed models [93]. Each outcome will be analyzed with a separate model with time modeled as person-specific (months since BL). We will explore linear, non-linear (i.e., logarithmic, exponential, quadratic), and piece-wise growth models to determine whether there are unique influences of STRIPES on time frames, reflected by slope over time; the best model will be selected using likelihood ratio tests. Effects of time, group, and their interaction will serve as model predictors, and covariates will be included.

#### Aim 3

Aim 3 tests three sets of mediational effects. The mechanisms by which STRIPES affects improvement in student outcome will be evaluated using a structural equation modeling framework in Mplus [94]. Significance of indirect effects will be assessed by bootstrap confidence intervals [95, 96]. In each model, variables that are repeatedly measured (i.e., outcomes, AM, observed EF, rewards processing, motivational strategy, and cognitive control) will be modeled with a mixed model as described in Aim 2. Aim 3a examines the effect of STRIPES on outcomes via AM and observed EF. Aim 3b examines the effect of STRIPES on AM via rewards processing and/or motivational strategy use. Aim 3c examines the effect of STRIPES on observed EF via cognitive control and/or motivational strategy use. For each model, STRIPES predicts the intercept and slope of the mediator model (a paths) and the intercept and slope of the outcome model (c’ paths), while the intercept and slope of the mediator model predict the intercept and slope of the outcome model (b paths).

Current recommendations advise evaluating mediators individually before combining them into a model with simultaneous mediators [97]. For example, Aim 3a will examine AM as a mediator of the STRIPES to outcome relationship in one model, EF as a mediator of the STRIPES to outcome relationship in a second model, and examine both variables as simultaneous mediators in a final model.

#### Aim 4

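### With 144 students, a and b paths of d = 0.35 give about 0.28–0.40 power for the Aim 3 indirect effect, not the sufficient power claimed

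*Protocol article*

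**What the plan says.** All statements are in the protocol article.

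- **Claim (Statistical power, Aim 3):** "With a sample size of 144 and using preferred bootstrap methods, we have sufficient power to detect the indirect effect provided both" paths pass a threshold, which the sentence sets by requiring that they "are greater than *d* = 0.35".
- **Basis:** for Aims 3a to 3c, "statistical power estimates are based on sample size calculations by" a cited mediation-methods paper. The section adds: "Statistical power for the indirect effect depends entirely on the values of the" a and b paths.
- **Expected effects:** earlier work is said to show a paths of d = 0.85 to 2.05 for Aims 3a and 3b. No expected b path is given for any of the three, and no a path is quoted under Aim 3c.
- **Sample size (Study timeline):** three annual cohorts at two schools, "12 per condition; total *N* = 144".
- **Attrition (Statistical power):** "We estimate 5% attrition based on previous studies".
- **Test (Data analysis plan, Aim 3):** "Significance of indirect effects will be assessed by bootstrap confidence intervals". The type of bootstrap interval is not named.
- **Benchmark:** Aim 3 has no numerical power target and no alpha. For Aim 2, the same section relies on a simulation paper that "found that statistical power exceeded 0.80 with samples of about 100 with medium or larger effects".

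**The concern.** To establish an indirect effect, the data must show both that treatment moves the mediator and that the mediator moves the outcome. Power for the product is therefore held down by the weaker path, and falls further when both are modest. A two-group difference of d = 0.35 with 72 per arm is known to be underpowered on its own, so sufficient power for the product at that value cannot be right.

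Mediation is how this trial addresses whether STRIPES remediates cognitive and reward deficits or builds compensatory skills (Study aims; Aims 3b and 3c). That distinction depends partly on which indirect effects are found and which are not. A reader who trusts the printed threshold could take a null indirect effect as evidence against a mechanism, when a true effect with both paths at d = 0.35 would be missed about 60% to 74% of the time.

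**Working it through.** **Inputs from the article.** N = 144. Arms: 12 per condition × 2 schools × 3 cohorts = 72 each. Threshold d = 0.35 on each path. Attrition 5%, so 144 × 0.95 = 136.8, about 137. Test by bootstrap interval.

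**Assumptions.** Two-sided alpha 0.05. Sufficient means 0.80, the Aim 2 benchmark. A b path in d is converted by r = d/√(d² + 4). Since the article rests power on a and b alone, no credit is given at first for baseline adjustment or repeated measures.

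**1. The a path alone** (normal approximation): power = Φ(d√(n/2) − 1.96), with n per arm.
- n = 72: 0.35 × √36 = 2.10; Φ(0.14) = **0.556**.
- n = 68.5: 0.35 × √34.25 = 2.048; Φ(0.088) = **0.535**.

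The exact t calculation gives 0.550 at n = 72. However strong b is, the indirect effect cannot do materially better: simulation with a raw b slope of 1.0 gave 0.55 (percentile) and 0.56 (bias-corrected). For 80% power on the a path alone, d = 0.35 needs 129 per arm.

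**2. The b path alone** (Fisher z for a partial correlation): r = 0.35/√(0.1225 + 4) = 0.172, atanh(r) = 0.174.
- N = 144: 0.174 × √140 = 2.06; Φ(0.10) = **0.540**.
- N = 137: 0.174 × √133 = 2.01; Φ(0.05) = **0.519**.

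**3. Both paths at d = 0.35.** Joint significance is the product: 0.556 × 0.540 = 0.30 at N = 144, and 0.535 × 0.519 = 0.28 at N = 137. The bootstrap figures come from simulating the single-mediator model (1,500 trials, 1,000 resamples each).

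| N | Joint significance | Percentile bootstrap | Bias-corrected bootstrap |
|---|---|---|---|
| 144 | 0.30 | 0.28 | 0.40 |
| 137 | 0.28 | 0.26 | 0.38 |

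**4. Attempts to recover the stated figure** (N = 144).
- One-sided alpha 0.05, joint: 0.675 × 0.661 = 0.45.
- a as d = 0.35, b as a standardised coefficient of 0.35: 0.55 joint by formula, 0.57 percentile, 0.65 bias-corrected.
- Baseline correlation of 0.7 sharpening both paths, joint: 0.69.
- Expected a path of 0.85 with b at d = 0.35: 0.54 joint, 0.55 percentile, 0.61 bias-corrected. At a = 2.05: 0.53, 0.54, 0.54.
- Both values read as standardised coefficients of 0.35: 0.96 to 0.98.

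Only the last gives 80%. For a balanced two-arm predictor, a standardised coefficient of 0.35 is d = 2r/√(1 − r²) = 0.70/√0.8775 = 0.75.

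**5. What 80% power requires.** With equal power on the two paths, each needs √0.80 = 0.894. By joint significance, both paths must be about d = 0.545 at N = 144 and about d = 0.56 at N = 137. The corresponding standardised coefficient at N = 144 is about 0.265. At d = 0.35 on both paths, about N = 342 would be needed.

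**The case against.** The best defence is that 0.35 is a standardised coefficient mislabelled as d. The b path relates two continuous variables, for which d is not the natural metric. On that reading power is 0.96 to 0.98, and the quoted a paths of 0.85 and above still exceed the equivalent d of 0.75. This may well be how the error arose, but the cited source is not available here, so it cannot be shown. It does not save the sentence: the article prints d and then compares the threshold with a paths expressed in d.

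A second defence is that 0.35 is only a lower bound and the expected a paths are far larger. This stands in part. For Aims 3a and 3b the realistic limit is the b path, and with a = 0.85 and b at d = 0.5 simulated power is 0.83 to 0.86. The one-in-three figure thus describes the threshold, not the expected trial. But the threshold is what the article asserts, and with b at that value power stays between 0.53 and 0.61 even with the quoted a paths.

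Three smaller points stand. N = 137 is a worst case, because full information maximum likelihood retains partly observed students. The article nowhere says a null indirect effect will be read as excluding a mechanism. Motivational strategy use is a mediator in both 3b and 3c, so part of Aim 3c may share a quoted a path. Missing b path values are detail a condensed article may leave to the full protocol and are not an error in themselves.

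**Conclusion.** The concern holds. As printed, the Aim 3 power statement is wrong: at N = 144 with both paths at d = 0.35, power is about 0.28 to 0.40 depending on the bootstrap interval, and 0.26 to 0.38 at N = 137. No variant examined that keeps the two-arm a path and the b path at d = 0.35 reaches 0.80.

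The exact figures rest on two-sided alpha 0.05, a 0.80 target, the d-to-r conversion for b, and a single-mediator model. The conclusion does not depend on the conversion, since the a path alone has power of about 0.55. The planned growth-model mediation may have different power, but the article rests its claim on a and b only.

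**What to change.** Replace the threshold sentence with one that names the metric, alpha, target power and type of bootstrap interval. For example: with 144 students and a two-sided 5% test, 80% power for the indirect effect requires both paths to be about d = 0.55 (standardised coefficient about 0.26) by percentile bootstrap or joint significance; at d = 0.35 on both paths, power is about 0.3 to 0.4. If the bias-corrected bootstrap is chosen, the threshold is nearer d = 0.50, where simulated power is about 0.78. If attrition is treated as complete loss, quote the N = 137 value, about d = 0.55 to 0.56.

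If a standardised coefficient of 0.35 was meant, say so and give its equivalent of d about 0.75 for the a path before comparing it with the earlier a paths.

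Two additions would help but are optional: state the assumed b path for each of Aims 3a to 3c in the same metric, and label Aim 3c exploratory where no earlier a path supports it.

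The cost is one paragraph and a less favourable detectable effect. Recruitment, data collection and the planned analyses do not change.

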### Study aims

This study first aims to engage school stakeholders to establish school-specific variations of the STRIPES implementation strategy that attend to developmental, disorder, and context-specific considerations and to document interventionist implementation fidelity (Aim 1). The CFIR will be used to guide the selection of questions for stakeholder interviews about potential barriers and facilitators to the implementation of STRIPES in the school context [46]. A randomized trial will then evaluate the impact of STRIPES (vs. enhanced school services control; SSU +) on target mechanisms including EF, AM, and student outcomes (GPA and class attendance; Aim 2). We will also estimate the extent STRIPES remediates cognitive control and rewards processing deficits, facilitates the development of compensatory skills that overcome the impact of deficits, or both. Aim 3 will explore whether differences in basic cognitive profiles moderate intervention response. The acceptability and feasibility of STRIPES will be examined with consideration of student, peer interventionist, and school stakeholder perspectives, and cost to schools (Aim 4). Lastly, we will investigate ecologically valid treatment moderators (baseline GPA, history of ADHD, disruptive classroom behavior, peer characteristics; Aim 5).

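### The Aim 5 statement of adequate power down to d = 0.245 rests on the seven best-powered of 35 pilot effects and is not supported for student-level moderators

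*Protocol article*

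**What the plan says.** Aim 5 is defined under Study aims: "we will investigate ecologically valid treatment moderators (baseline GPA, history of ADHD, disruptive classroom behavior, peer characteristics; Aim 5". Its power is argued in the Statistical power section of the protocol article, from the previous 72-student STRIPES trial:

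- Source of the non-centrality: "We used F statistics to estimate the non-centrality parameter".
- Degrees of freedom: the authors "estimated a denominator degrees of freedom based on more observations (144 students each measured 5 times versus 72 students each measured 4 times").
- Result: "Of the 35 effects examined, the mean power value was 0.61", with seven effects above 0.80.
- Conclusion: "based on the non-centrality parameters for these effects, we have adequate power to detect effects as small as" Cohen's d = 0.245, which the section calls small.

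The number of students does not depend on this argument. Power is assessed "given a fixed sample size of 144".

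**The concern.** The closing sentence reads as a property of the trial, yet it is derived only from effects picked out because their power was high. Three features make it doubtful.

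- **Selection.** Four fifths of the effects examined did not exceed 0.80, and the conclusion does not carry that qualification.
- **Observed F as non-centrality.** With one numerator degree of freedom, an observed F exceeds the true non-centrality by about 1 on average. Taking the largest of 35 makes this worse.
- **Unit of information.** Baseline GPA, history of ADHD and disruptive behaviour vary between students. Five measurements on one student are not five independent observations on that student's moderator value. A moderator effect is also a difference between two treatment effects, which is estimated less precisely than one treatment effect.

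At stake is how null moderator results are read. With d = 0.245 on record, a non-significant interaction could be taken as well-powered evidence that STRIPES works alike across subgroups. The article does not say that it will be used in that way.

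**Working it through.** **Inputs from the article.** 144 students. Per arm, 12 per condition × 2 schools × 3 cohorts = 72 ("24 9th grade students will be recruited at each of the two schools (12 per condition", Study timeline). "We estimate 5% attrition based on previous studies", so 144 × 0.95 ≈ 137. Observations: 144 × 5 = 720.

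**Assumed, because not stated.** Two-sided alpha 0.05; equal correlation ρ between any two measurements on a student, from 0.1 to 0.9; a binary moderator split 50/50, giving 36 students per cell; outcome SD of 1.

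**Step 1. The plan's own counts.** 35 − 7 = 28, and 28/35 = 80% did not exceed 0.80. Total power is 35 × 0.61 = 21.35. If the seven lie between 0.80 and 1.00, the other 28 average between (21.35 − 7.0)/28 = 0.51 and (21.35 − 5.6)/28 = 0.56.

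**Step 2. Trying to reproduce 0.245.** For two equal groups of N units in total, the non-centrality is λ = N·d²/4, with d² = 0.0600.

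- 80% power at 1 df needs λ ≈ (1.960 + 0.842)² = 7.85, so N = 4 × 7.85/0.0600 ≈ 523 independent units.
- N = 720: λ = 10.80; power 0.91 at 1 df, 0.79 at 3 df.
- N = 144: λ = 2.16; power 0.31 at 1 df, 0.20 at 3 df.

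So 0.245 is the size of figure that an observation-level count gives, and not what 144 independent units give. The match to 80% at 720 needs 3 numerator df, which the article does not state. The figure is therefore not reproduced.

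**Step 3. Simple two-arm difference, one measurement.** SE = √(2/72) = 0.167. Then 0.245/0.167 = 1.47, and power is about 0.31. The detectable d at 80% power is 2.802 × 0.167 = 0.47. At 137 students these become 0.30 and 0.48.

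**Step 4. Balanced moderator, 144 students.** The SE of the difference in treatment effects is √v × √(4/36) = √v/3, so the detectable difference is 2.802 × √v/3 = 0.934√v. The variance factor v depends on the contrast:

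- mean of five measures: v = (1 + 4ρ)/5
- change score, mean of four later measures minus baseline: v = 1.25(1 − ρ)
- baseline-adjusted mean of m later measures (m = 5 or 4): v = [1 + (m − 1)ρ]/m − ρ²

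| ρ | mean of five | change score | baseline-adjusted (m = 5 / 4) |
|---|---|---|---|
| 0.1 | 0.49 | 0.99 | 0.49 / 0.52 |
| 0.5 | 0.72 | 0.74 | 0.55 / 0.57 |
| 0.8 | 0.86 | 0.47 | 0.42 / 0.43 |
| 0.9 | 0.90 | 0.33 | 0.31 / 0.32 |

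Power for a difference of 0.245 runs from 0.11 (change score, ρ = 0.1) to 0.60 (baseline-adjusted, m = 5, ρ = 0.9).

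**Step 5. What 0.245 would need.** v = (0.245/0.934)² = 0.069. The change score reaches this at ρ = 1 − 0.069/1.25 ≈ 0.945, and the baseline-adjusted contrast at about 0.94. The five-measure mean does not reach it at any non-negative ρ: at ρ = 0, v = 0.2 and the detectable difference is 0.934 × √0.2 = 0.42.

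**The case against.** **The two figures are compatible.** A reader might infer that mean power of 0.61 contradicts d = 0.245. It does not. The mean averages over the effects seen in the pilot, whereas 0.245 is a detectability threshold. Both hold if most pilot effects were smaller. The article also prints the 0.61 and the seven of 35 openly. This stands.

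**A threshold can be read from selected effects.** If all 35 tests had the same precision, the smallest effect with power above 0.80 would be a fair threshold for all of them. The article does not show common precision, and does not say that the seven were moderator effects.

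**Counting 720 observations is an inference.** The article says only that the denominator degrees of freedom reflect more observations. How the non-centrality was scaled and converted to d is not given, and 0.245 could be a partial effect size on another scale than a raw SD difference. This stands, so the point has to be that the figure is unsupported, not that its error has been located.

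**Precision depends on the model.** It would go too far to say that 144 students cannot deliver 0.245. For a main effect the required v is (0.245/0.467)² = 0.275, which a change score meets at ρ ≈ 0.78 and a baseline-adjusted mean at about 0.69 to 0.71. For a moderator, a very high correlation would suffice. Baseline GPA is continuous, so the 50/50 split is only a convenient case.

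**Consequence.** Aim 5 comes last among the aims and sets neither the sample size nor a decision rule. This lowers the severity but does not make the sentence correct.

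**Conclusion.** The sentence is wrong as written, at moderate to low severity. It turns the best-powered fifth of the pilot effects into a general property of the trial, and the printed derivation does not support that for student-level moderators.

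Under the assumptions listed, 0.245 has power of about 0.31 as a simple two-arm difference. For a balanced student-level moderator it does not reach 80% power at any correlation tried up to 0.9; the smallest detectable difference in that range is 0.31 and the largest 0.99.

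The selection argument needs only the article's own counts. The size of the shortfall depends on alpha, the correlation, the contrast and the moderator split, none of which is stated.

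A further tempting reading is that peer characteristics cannot be moderators at all, since peer interventionists are described for STRIPES while the Comparison section describes a counselor referral. That follows only if the term means the interventionists' own characteristics, and the article does not define it.

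**What to change.** 1. Withdraw the general d = 0.245 statement.
2. Replace it with wording such as: Aim 5 is exploratory; of 35 effects of the size seen in the previous trial, 28 did not exceed 0.80 power (mean 0.61), so absence of a significant interaction will not be read as evidence of equal benefit.
3. Recompute the detectable group-by-moderator effect at student level, for 144 students and for about 137 after attrition. State alpha, numerator degrees of freedom, within-student correlation, the contrast and the moderator distribution. Give the result over a range of correlations; one fixed figure or range without these assumptions would repeat the problem.
4. Define peer characteristics. If these are the interventionists' characteristics, analyse them as predictors within the STRIPES arm (n = 72), not as group-by-moderator terms.

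The cost is wording and a short recalculation. No further students or data are needed. The drawback for the sponsor is a less favourable stated figure.
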